### 2.5. Control Condition

For each participant, the CC consists of indications to websites specifically focused on the different psychological conditions (depression, anxiety, sleep problems, self-disruptive thoughts, job- and study-related stress and burnout, and chronic pain) they report as areas of distress according to the global screening.

### 2.6. Outcome Measures

Participants will be screened with a complete online battery to assess their symptoms, including both primary and secondary outcome measures, at pretreatment baseline (T0), after the 7-week IB-MAI treatment, or CC completion (T1), at 12-week follow-up (T2), and 24-week follow-up (T3) (see Figures S1 and S2 for the study design and assessments). Moreover, at pretreatment time (T0), socio-demographic questions are included; these concern marital status, educational qualification, employment status, physical or psychiatric illnesses, and past or current therapies. Questions related to gender and the COVID-19 pandemic are included to investigate the influence of the pandemic on students’ mental health status. These items were drawn up according to the International COVID-19 Suicide Prevention Research Collaboration guidelines [56]. In contrast, those relating to gender were taken from the Williams Institute of the UCLA School of Law for health surveys [57].

Since participants have a timeframe to begin and complete each week of treatment, the overall treatment duration can differ among subjects. Therefore, post-treatment and follow-up time points will be calculated for each participant, starting from the end of the last activity.

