### 2.3. RCT Design

This study will be conducted in accordance with the Consolidated Standards Of Reporting Trials (CONSORT) checklist for the RCT design [34]. Participants will be randomly assigned following blind simple randomization procedures when they complete the baseline assessment (randomization sequence under computer control adopting computerized random numbers) to 1 of 2 treatment groups (see Figures S1 and S2 for the study design and assessments). We only keep the 1:1 ratio constraint at the 260th participant, meaning that when one group reaches 130 participants, all the remaining volunteers (up to the total of 260) will be allocated to the other group. Students will be randomized to IB-MAI or CC. Participants in the intervention condition will receive an 8-week unguided IB-MAI program, i.e. MindBlooming. Participants in the CC condition will access websites with information about their specific areas of distress identified at baseline. Participants will be assessed with repeated measures (baseline, 8 weeks, 12 weeks, and 24 weeks). The RCT participants’ flow is presented in Figure 2.

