Every week for the entire duration of the intervention, participants will have access to one session per module, except for the 6th week, which is dedicated to the treatment of relational problems: regardless of the specific issue (depression or anxiety, etc.), this training deals with relational issues relevant to everyone, hence the importance of transversally proposing it. The modules will be presented as follows:○1st week: module 1 and 2 sessions;○2nd week: module 1 and 2 sessions;○3rd week: module 1 and 2 sessions;○4th week: module 1 and 2 sessions;○5th week: module 1 and 2 sessions;○6th week: relational problems related to difficulties in emotion regulation and empathy deficits session;○7th week: module 1 and 2 sessions about relapse prevention, future planning by reflecting on how to attain goals and implement behavioral changes, orientation, and conclusion.

All online sessions will include psychoeducational videos (brief seminars of 15 min each, with audios and PowerPoint presentations), about epidemiology, explanatory models, risk and protection factors, treatments, and some specific aspects of each psychological issue. Once the videos have been seen, training exercises will be proposed to help participants to integrate the content of the sessions into their daily lives (Figure 3). Contents and approaches used for each module are further presented in Table 1.

Quizzes will be presented during each session, along with the possibility for the participants to reply and insert text. Subsequent sessions will be available only if the previous session, and a minimum of related exercises, is completed within 7 days (+3 days to be flexible in the case of students unable to maintain the pace). Even if the contents are completed before the 7th day from the start, new contents will be available from the 7th day onwards. When a new week of treatment is available, participants have 3 days to start completing the tasks. If the subjects do not respect the deadlines, they will be excluded from the study. Participants also have access to a list of available supplementary resources.

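### Assessments are set at fixed weeks in one section and timed from each participant's last activity in another, with control T1 undefined, so the arms can be measured at different elapsed times

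*Protocol article*

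**What the plan says.** Section 2.3 (RCT Design) gives one schedule and does not distinguish the arms: "Participants will be assessed with repeated measures (baseline, 8 weeks, 12 weeks, and 24 weeks". It also states the length of the programme: "Participants in the intervention condition will receive an 8-week unguided IB-MAI program".

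Section 2.6 (Outcome Measures) places the assessments "after the 7-week IB-MAI treatment, or CC completion (T1), at 12-week follow-up (T2), and 24-week follow-up (T3". It then notes that, because each treatment week has a window for starting and finishing, "the overall treatment duration can differ among subjects", and concludes that "post-treatment and follow-up time points will be calculated for each participant, starting from the end of the last activity". The Abstract, the week-by-week list in section 2.4 and section 2.6 all describe a 7-week programme.

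The windows themselves are in section 2.4 (Intervention). The next session opens only if the previous one, with a minimum of its exercises, "is completed within 7 days (+3 days to be flexible in the case of students unable to maintain the pace". However early a week is finished, "new contents will be available from the 7th day onwards". Once a week opens, "participants have 3 days to start completing the tasks". Participants who miss the deadlines are excluded.

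Section 2.5 (Control Condition) describes the control arm only as pointers to websites on the participant's areas of distress. It mentions no sessions, tasks, deadlines or end point.

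Section 2.8 (Statistical Methods) compares the T0 to T1 changes of the two arms with t-tests and their Bayesian counterparts. It then uses T1, T2 and T3 as within-subject levels, with arm as the between-subjects factor, in a mixed ANOVA.

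**The concern.** Sections 2.3 and 2.6 are both current text, and they give different rules for when the outcome is measured. An assessment falls either at a fixed week or at an individually floating date.

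The floating rule is justified by windows that govern app sessions. In the app arm it makes the date of T1 depend on the participant's pace, which is behaviour after randomisation. In the control arm it depends on a completion event with no definition. Randomisation does not balance a timing rule that operates differently in the two arms, and neither the t-tests nor the ANOVA described in section 2.8 contain a term for elapsed time.

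At stake is the interpretation of the between-arm difference in T0 to T1 change. If one arm is measured systematically later, spontaneous change since baseline enters the treatment contrast. That student stress, burnout, anxiety and sleep change over a few weeks, for instance around examinations, is my assumption; the article gives no data on it.

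**Working it through.** **Inputs.** Seven weekly steps (section 2.4). A new week opens no earlier than day 7 after the previous one. Each week may take up to 7 + 3 = 10 days. The fixed schedule is 8, 12 and 24 weeks (section 2.3). Three assumptions are needed: the weeks in section 2.3 count from baseline; treatment starts at baseline, since participants are randomised on completing that assessment; and T1 is taken on the day of the last activity.

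**The plan's own length.** 7 weeks × 7 days = 49 days = 7 weeks. This reproduces the 7-week figure. The 8-week figure in section 2.3 is 56 days and does not follow from the weekly list.

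**Last activity in the app arm.**

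- Earliest: week *k* opens on day 7(*k* − 1), so week 7 opens on day 7 × 6 = 42 and may be finished at once. That is 6 weeks.
- Latest, with the 3-day start window inside the 10 days: 7 × 10 = 70 days, or 10 weeks.
- Latest, if the start window is additional: 7 × (10 + 3) = 91 days, or 13 weeks.

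T1 therefore spans about 6 to 10 weeks, a range of 70 − 42 = 28 days, against a fixed 8 weeks (day 56). A participant who uses all three extra days on three of the seven weeks and takes 7 days over each of the others finishes on day 4 × 7 + 3 × 10 = 58, already after day 56.

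**T2 and T3.**

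| Assessment | Section 2.3 | Section 2.6, counted from last activity | Difference |
|---|---|---|---|
| T1 | week 8 | weeks 6 to 10 | −2 to +2 weeks |
| T2 | week 12 | weeks 6 + 12 = 18 to 10 + 12 = 22 | 6 to 10 weeks |
| T3 | week 24 | weeks 6 + 24 = 30 to 10 + 24 = 34 | 6 to 10 weeks |

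With the additional start window, the upper limits become weeks 13, 25 and 37. A T1 at week 13 would then come after the week-12 assessment of section 2.3.

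**Spacing for the stability analysis.** Under section 2.3 the T1–T2 gap is 12 − 8 = 4 weeks and the T2–T3 gap is 24 − 12 = 12 weeks. Counted from last activity, both gaps are 12 weeks. If T1 floats but T2 stays at week 12 from baseline, the T1–T2 gap is 12 − 10 = 2 to 12 − 6 = 6 weeks. The ANOVA's time factor means something different under each reading.

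**Control arm.** Section 2.6 names completion of the control condition as its T1. Section 2.5 describes nothing that can be completed. No date, and hence no elapsed time, can be computed.

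**The case against.** The strongest reply is that assessing each participant at the end of their own treatment is a recognised design, and that a condensed article may leave the control-arm calendar to supplementary Figures S1 and S2, which both sections cite and which are not shown. A single line equating control completion with the 8 weeks of section 2.3 would supply the missing anchor. This stands in part: the control anchor is named but undefined, so it would be wrong to say that none exists. It does not remove the conflict between sections 2.3 and 2.6, because a figure cannot make two contradictory statements in the text agree. Nor would a fixed 8 weeks for controls align the arms while the app arm floats between about 6 and 10.

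A reader might go further in three ways that the text does not support.

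- That someone who stops in week 2 would have T1 in week 2. Section 2.4 excludes participants who miss the deadlines, so such a person may have no T1 at all. That raises a separate question about exclusion after randomisation.
- That the arms will be measured at different times. The control timing is unknown and section 2.3 does give a common schedule, so the text supports only that they can be.
- That T1 has to be on day 70 or later. Day 70 assumes that the start window lies within the 10 days, and a late fixed T1 changes the question from effect at the end of treatment to effect at a set time. That is a choice for the trial team.

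**Conclusion.** The point holds as an inconsistency that bears on the main between-arm comparison. The article gives two incompatible timing rules, applies one of them through an event that it does not define for the control arm, and states two programme lengths.

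By its own windows, T1 in the app arm can vary by about 4 weeks, and the two readings of T2 and T3 differ by 6 to 10 weeks. These ranges rest on the assumptions listed with the calculation, chiefly that the start window is not additional; if it is, the upper limits move out by 3 weeks.

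Whether this would bias the treatment contrast, by how much and in which direction cannot be derived from the document. The sample size calculation does not depend on it.

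**What to change.** Time T1, T2 and T3 from the date of randomisation, at the same weeks and with the same permitted window in both arms, and state that origin in sections 2.3 and 2.6. Replace the last-activity rule for the between-arm analyses. Choose a T1 week that is consistent with the programme's own completion windows, and say whether the 3-day start window lies within the 10 days or is added to them. Reconcile the 7-week and 8-week programme lengths across the Abstract and sections 2.3, 2.4 and 2.6. If an end-of-treatment assessment in the app arm is also wanted, it can be kept as a within-arm measure.

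The cost is reprogramming the dates of online questionnaires. Fast finishers would be assessed some weeks after their last session: up to 70 − 42 = 28 days, about 4 weeks, if T1 were set at day 70, and less if it were set earlier. An earlier T1 would instead find the slowest participants still in treatment.

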#### 2.6.1. Primary Outcome Measures

❖Beck Depression Inventory (BDI-II) [58,59], composed of 21 items investigating depressive symptoms (see Supplementary File S1 for a thorough description of the scales).❖State-Trait Anxiety Inventory (STAI) [60,61], consisting of 40 items exploring state and trait anxiety.❖Italian Version of the Pittsburgh Sleep Quality Index (PSQI) [62,63], consisting of 19 items to investigate sleep quality in the last month.❖Brief version of the Columbia-Suicide Severity Rating Scale (C-SSRS) [64] modified, consisting of 4 items investigating current suicide risk and 5 items investigating lifetime risk.❖School Burnout Inventory (SBI) [65,66], composed of 9 items exploring three dimensions of burnout, i.e., exhaustion, cynicism, and sense of inadequacy.❖Difficulties in Emotion Regulation Scale (DERS-20) [67,68] consisting of 20 items investigating emotional regulation skills, and the Brief Interpersonal Reactivity Index (B-IRI) [69,70], consisting of 16 items investigating empathic response skills.❖Brief Pain Inventory (BPI) [71,72], composed of 15 items measuring the intensity of pain and its impact on daily functioning.❖World Health Organization Quality of Life—short version (WHOQOL-BREF) [73], consisting of 26 items investigating the quality of life.

#### 2.6.2. Secondary Outcome Measures

❖Visual Analogue Scales (VAS) for psychological and physical pain (6 items) [32].❖Insomnia Severity Index (ISI) to investigate the impact of insomnia in the last two weeks (7 items) [74].❖Toronto Alexithymia Scale (TAS-20), consisting of 20 items investigating levels of alexithymia [75,76].❖Coping Orientation to the Problems Experienced (COPE-NVI-25) [77,78], consisting of 25 items investigating coping strategies.❖Life Events Checklist (LEC) [79], composed of 16 items investigating the subject’s stressful experiences.❖Reasons for Living Inventory (RFLI) [80], consisting of 48 items investigating the subject’s reasons for living.❖COVID-19-related questions compiled according to the International Association for Suicide Prevention (IASP) guidelines for suicide prevention research [56].

Given the feasibility nature of this study, data on the program’s acceptability will also be collected at post-treatment (T1) through the same measures used in the pilot study and described in the related paragraph.

### 2.7. Sample Size Calculation

Considering the attrition rate, we will recruit 260 students to obtain 200 study completers. A total of two-hundred participants will allow to detect an effect size of at least d = 0.40, fixing a power (1 − β) of 80%, and an alpha of 0.05 (two-tailed) in a between group comparison (e.g., comparing the two treatments). This sample size is similar to Harrer et al. [25]. The effect size is estimated considering a recent meta-analytic review for Internet-based stress interventions which reports effect sizes ranging between d = 0.32 and d = 0.64 [81].

Frequentist and Bayesian approaches have their own advantages and drawbacks in data analysis. We will adopt both to provide robust evidence to the specific statistical approach.

We conducted a Bayes Factor Design Analysis (BFDA) [82] (i.e., the counterpart of power analysis in the Bayesian world) to estimate the Bayesian analysis sensitivity, given the sample size of 200 people. We simulated 10,000 results, fixing the Bayes Factor (BF) decision boundary at 10, and an estimated effect size for a true H1 equal to d = 0.40. The BFDA simulation was performed for a default prior (i.e., a Cauchy distribution with a scale = 0.707) and an informative prior (i.e., a t distribution with μ = 0.35, df = 3, r = 0.102), considering true H0 (i.e., d = 0) and H1 (d = 0.40). Given those parameters, we estimate to surpass the decision boundary for H1 in 87.8% adopting the default prior and 93.8% of the case adopting the informed prior. In the case of a true H0, the decision boundary is surpassed in 45.5% and 62.2% of the cases adopting the default or the informed prior, respectively. The design is robust to the misleading evidence, showing a false positive evidence rate of 0.002 and 0.006 adopting the default or the informed prior. No false negative evidence has been observed over 10,000 simulations with any of the two priors. In the case of inconclusive evidence, we will increase the sample size until the BF decision boundary is surpassed (BF > 10) in either one of the two directions supporting H1 or H0.

We expect to have enough data to tune a model that highlights treatment response predictors and different trajectories in students’ response to treatment. We will test five different algorithms: Linear Discriminant Analysis (LDA); Classification and Regression Trees (CART); k-Nearest Neighbors (kNN); Support Vector Machines (SVM) with a linear kernel; and Random Forest (RF). This will offer a good mixture of simple linear (LDA), non-linear (CART, kNN), and complex non-linear methods (SVM, RF).

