### 2.4. Intervention

MindBlooming is conceived as an Internet-Based Multi-Approach Intervention (IB-MAI) intended to provide psychoeducation and teach new strategies to cope with different psychological problems. We consider MindBlooming to be multi-approach since it integrates different psychotherapeutic strategies such as Cognitive Behavioral Therapy [35], Acceptance and Commitment Therapy [36], Mindfulness-Based Cognitive Therapy (MBCT) [37,38], Mindfulness-Based Stress Reduction (MBSR) [39], and Dialectical Behavioral Therapy [40]. All these interventions are evidence-based and several studies proved their efficacy in treating different psychological conditions (for an overview, see [41] and APA division 12 list of research-supported psychological treatments, https://div12.org/psychological-treatments/, accessed date 29 December 2021). The intervention consists of 6 interactive modules: depression, anxiety, sleep problems, self-disruptive thoughts, job- and study-related stress and burnout, and chronic pain. A total of two modules will be assigned to each participant based on the initial screening and specific requests and preferences. In addition to the assigned treatments based on the initial screening, all participants will receive a separate training to improve their relational and empathy skills: during the 6th week, they will have access to two videos focused on the importance of relationships on our health, social support as a protective factor, social isolation and loneliness as a risk factor, emotion regulation, and empathy. Afterward, they will have access to a set of exercises, including quizzes about social relationships, assertive communication training, DBT [40], and Interpersonal Psychotherapy (IPT) for Depression strategies (which correlate depressive symptomatology to relational problems) [42]. Moreover, during the 7th week of treatment, more contents in the same formats (videos, texts, and quizzes) will be proposed, focusing on emotions and relationships problems related to the specific issues faced in the assigned modules (e.g., problems in relationships in association with depressive symptoms).

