### 2.8. Statistical Methods

Statistical analyses will be conducted adopting both a frequentist and a Bayesian approach to provide robust evidence favoring or against the intervention.

The main study outcome is to verify the effectiveness of the intervention: this would be verified by a T0 to T1 delta different from 0. Additionally, we will test the effectiveness of the IB-MAI against the CC group comparing the two T0 to T1 deltas. We will use a series of *t*-tests and its Bayesian [83] corresponding test.

Stability over time will be verified with a mixed ANOVA using the T1, T2 and T3 datapoints as within-subject measures and group (IB-MAI versus CC) as a between-subjects factor. We will use “classic” (i.e., frequentist) ANOVA and its corresponding Bayesian version [84] for each primary and secondary outcome measure.

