For what concerns the predictive model, we will explore the possibility to use ML algorithms to tune a model able to predict the responders on each of the primary outcomes starting from the socio-demographic information collected and the primary and secondary outcome measures in two steps. First, we will use only socio-demographic information to predict the primary outcome measure of each module. Second, we will use the socio-demographic information, the other primary, and all the secondary outcome measures to predict the primary outcome of each specific module. Before entering an outcome measure as a target variable (i.e., to be classified/predicted variable), variables have to be dichotomized. We will classify participants as responders or non-responders, adopting the minimum clinical importance difference and adopting a distribution approach [85]. A responder will be defined as a participant that records a change larger than 1 standard error of the mean (SEM) calculated on the baseline distribution. For example, the effectiveness of the first module is measured primarily on the BDI-II scale. We will first identify participants that change more than 1 SEM to classify responders and non-responders. Then we will use ML algorithms to predict this outcome starting from socio-demographic in a first step, and socio demographic plus the other outcome variables (except BDI-II of course) in a second step. We will test five different algorithms to have a good mixture of simple linear (LDA), nonlinear (CART, kNN), and complex nonlinear (SVM, RF) methods, thus covering the most used and diffused ML methods [86]. A total of 20% of the data will be held out for testing purposes, thus ML training will be performed on the remaining 80% data of the total sample. The portion of sample holdout will be set at the beginning and kept constant for all the algorithms tested and outcomes targeted, to make the different models’ performances directly comparable.

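### Nine unranked primary scales with no success rule, but 200 completers justified for a single comparison at alpha 0.05: the stated error rate and 80% power do not both carry over to the primary analysis

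*Protocol article*

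**What the plan says.** All references are to the protocol article.

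- **Sample size (section 2.7).** "A total of two-hundred participants will allow to detect an effect size of at least d = 0.40", "fixing a power (1 − β) of 80"%, with "an alpha of 0.05 (two-tailed) in a between group comparison (e.g., comparing the two treatments"). The effect size is taken from "a recent meta-analytic review for Internet-based stress interventions which reports effect sizes ranging between d = 0.32 and d = 0.64". Recruitment is 260, to leave 200 completers.
- **Primary outcomes (section 2.6.1).** Eight bullets hold nine scales: BDI-II, STAI, PSQI, C-SSRS, SBI, DERS-20, B-IRI, BPI and WHOQOL-BREF. One bullet pairs "Difficulties in Emotion Regulation Scale (DERS-20) [67,68] consisting of 20 items investigating emotional regulation skills" with the B-IRI. No scale is singled out.
- **Hypothesis (Aims and Hypotheses).** Superiority over control is expected on primary and secondary measures alike. The text does not say whether one, some or all must succeed.
- **Analysis (section 2.8).** The arms are compared on the T0 to T1 change by a series of t-tests and their Bayesian counterparts. The phrase "for each primary and secondary outcome measure" belongs to the later mixed ANOVA on T1 to T3, not to these t-tests.
- **Treatment received (section 2.4).** "A total of two modules will be assigned to each participant based on the initial screening and specific requests and preferences". There are six modules. The relational and empathy training goes to everyone.
- **Link between scale and module (section 2.8, predictive model).** "the effectiveness of the first module is measured primarily on the BDI-II scale".
- **Measurement (section 2.6).** Every participant completes the whole battery.

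**The concern.** A sample size for one test supports one confirmatory claim. Here nine scales share primary status, and the article does not say how nine results become one conclusion. Without a rule, a single significant scale among nine could be reported as a positive trial although chance alone makes that fairly likely. With a correction, the promised 80% is no longer available.

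A second issue concerns what d = 0.40 refers to. Six of the scales correspond to optional modules, and a student works on only two. If such a scale is compared across all 200 completers, many of them may not have worked on that problem, and the average effect could be well below 0.40. A null result on, say, the BPI could then not be told apart from dilution.

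**Working it through.** **Inputs.** From section 2.7: d = 0.40, two-sided alpha 0.05, 200 completers. From section 2.3: 1:1 allocation, so about 100 completers per arm. From section 2.6.1: k = 9 scales, each counted as one test. From section 2.4: two of six modules. Assumed because the article does not give them: the correlation between scales, the share of students in each module, and the effect in students without the module.

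**1. The plan's own figure.** The noncentrality is d × √(n/2) = 0.40 × √50 = 2.83. The normal approximation gives Φ(2.83 − 1.96) = 80.7%; the two-sample t-test gives 80.4%. The required size is 99 to 100 per arm. The stated 200 is reproduced for a single test in which d = 0.40 holds for the whole sample.

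**2. Any one success counts, no adjustment.** Under independence, familywise error is 1 − 0.95⁹ = 37.0%. Simulation with a common correlation between the nine test statistics gives:

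| Assumed correlation | Familywise error |
|---|---|
| 0 | 37% |
| 0.3 | 33% |
| 0.5 | 27% |
| 0.7 | 20% |
| 0.9 | 12% |

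**3. Any one success counts, Bonferroni.** The per-test alpha is 0.05/9 = 0.0056, with critical z = 2.77. Power per scale at d = 0.40 and 100 per arm is Φ(2.83 − 2.77) = 52% by the normal approximation and 51% by the t-test. The d detectable with 80% power is about 0.52.

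**4. All nine must succeed.** Each test may keep 0.05, so alpha is not inflated. Joint power, if the tests are independent and each has 80%, is 0.80⁹ = 13%. Correlation would raise this.

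**5. Dilution scenario, module scales only** (BDI-II, STAI, PSQI, C-SSRS, SBI, BPI). Let p be the share of students in the module and s the fraction of the effect that reaches the others. The full-sample effect is 0.40 × [p + (1 − p)s], with the SD taken as unchanged. Power is for 100 per arm at unadjusted 0.05:

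| p | s | Full-sample d | Power |
|---|---|---|---|
| 1/3 | 0 | 0.13 | 16% |
| 1/2 | 0 | 0.20 | 29% |
| 2/3 | 0 | 0.27 | 47% |
| 1/3 | 1/2 | 0.27 | 47% |

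The share of 1/3 is what an even spread of two modules out of six would give. Analysing a scale only in students with its module, at that share, leaves about 33 per arm and 36% power at d = 0.40.

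**The case against.** Several points on the other side have force.

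- **A statistical analysis plan may hold the multiplicity rule and the analysis set for each scale.** That is a normal division of labour, and their absence from the article is not itself the fault. But the article fixes the sample size at unadjusted 0.05. A Bonferroni-type rule added elsewhere would bring the stated 80% down to about 51%.
- **The alpha inflation depends on the success rule.** If all nine scales must succeed, there is none. That is correct, and step 4 shows that power is then what fails.
- **The Bayesian analysis looks better protected.** Section 2.7 gives false-positive rates of 0.002 and 0.006 at a Bayes factor of 10. Over nine independent tests these become 1 − 0.998⁹ = 1.8% and 1 − 0.994⁹ = 5.3%. But no rule says which framework decides, and the 80% at alpha 0.05 is a frequentist claim. Section 2.7 also lets the sample grow if evidence is inconclusive, so the power figures above are for a fixed 200.
- **Spill-over between modules is plausible.** Table 1 lists the same six exercises for depression and anxiety, and three of these recur in the self-disruptive thoughts and chronic pain modules. The introduction calls the treatment transdiagnostic. Zero spill-over is therefore the extreme case.

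A reader might also infer more than the text supports:

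- *Every primary scale will be tested at 0.05 in all participants.* This is not stated. It is an inference from the common battery, the 200-person comparison and the lack of any restriction.
- *Dilution affects all nine scales.* DERS-20 and B-IRI match training given to everyone, and WHOQOL-BREF is generic. The explicit link of a scale to a module comes from the predictive-model paragraph, not from the efficacy analysis.
- *Power on a module scale is 16%.* That needs an even spread and no spill-over. Modules follow screening, requests and preferences, and no shares are given.
- *C-SSRS lifetime items would enter the change score.* Nothing in the article says so.

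**Conclusion.** The concern holds in this form: the sample-size statement is correct for one comparison and does not describe a primary analysis with nine unranked scales. None of the three success rules examined delivers both a 5% error rate and 80% power:

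- unadjusted, any one success: familywise error 12% to 37%, depending on correlation;
- Bonferroni over nine: 51% power per scale at d = 0.40;
- all nine required: 13% joint power if independent.

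These rest on 100 completers per arm and d = 0.40 on each scale in the whole sample.

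Dilution is a supported risk for six scales, but its size is unknown. The scenarios run from 16% to 47% power in the full sample. Restricting a scale to its own module does not escape the problem at a one-third share (36%).

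**What to change.** Choose one of two routes.

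1. **One primary outcome.** Name in advance a single between-group T0 to T1 outcome that uses all participants, and make the other scales secondary. One option is each participant's baseline-standardised score on a module scale, fixed and recorded in both arms before randomisation and analysed with adjustment for baseline score and module. The article does not rank a student's two modules, so this option needs a written rule for which scale counts. It is one possibility, not the only sound choice.
2. **Keep nine primaries.** Apply Holm to the nine between-group T0 to T1 tests. Restate section 2.7 as about 51% power per scale at d = 0.40 at the first Holm step, or a detectable d of about 0.52 for 80% power.

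Under either route, state that the power figure assumes d = 0.40 across the whole sample.

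The cost is wording, plus a stored code per participant if the module-scale option is used. Single-scale claims become secondary (route 1), or the stated power becomes less favourable (route 2). No extra participants are needed.
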